### Ethical approval

This study has received ethical approval from the research ethics committee at GUH (ref CA 864).

## Trial management and quality control

### Clinical site

This single-center study will be conducted at Croí House, and the coordinating center will be located at the HRB-CRFG, National University of Ireland, Galway.

### Data collection and quality control

All data collection and all study-outcome measurements are conducted locally. Data are entered into an electronic case-report form by the attending researcher. Data entered include participant identification numbers, verification of eligibility criteria, verification of written informed consent, relevant participant demographic and clinical characteristics, current medications, physical parameters such as blood pressure and BMI, adherence to follow-up, adherence to the intervention, and questionnaire scores. All questionnaire scores are recalculated to ensure validity. Laboratory results for HbA1c, lipoproteins, and eGFR will be automatically entered into the GUH database and will be manually entered into the electronic case-report forms and trial database.

All study personnel are blinded to study-group assignment and will remain blinded until all data have been collated, entered into the database, the full dataset has been blindly reviewed for errors, and statistical analyses have been completed. Blinding will thus help to avoid differential measurement bias or biased data entry.

To ensure that high-quality data are collected, staff receive training on completing case-report forms. In addition, central statistical monitoring of the data by using data-entry edit checks is used, to improve the validity of the data-entry process.

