### Blinding

Trial participants, investigators, data collectors, statistician, and outcome assessors are blinded to study-group assignment. Members of the Sleepio team assigning participants to treatment groups are not blinded. Participant consent forms and information leaflets state that a behavioral lifestyle intervention is being compared with a control, and describe the intervention as general education on cardiovascular risk factors. It is also mentioned that aspects of the intervention are delivered via online web sessions, as well as through face-to-face sessions. Cardiology research nurses deliver the usual care intervention (that is, the cardiovascular education intervention) to participants in both treatment arms.

All laboratory measurements are carried out in a blinded fashion. Laboratory samples, with the exception of HbA1c serum levels, are frozen and then stored, and will be analyzed at the end of the trial. Serum HbA1c levels are measured on the day of collection. Blood pressure measurements are recorded in a blinded fashion by using a 24-hour automated blood pressure monitor, thus avoiding observer bias. All other study measurements, including BMI and questionnaire scores, are interpreted and entered into the study database in a blinded fashion by a trained researcher. Because of the nature of the intervention, a requirement for breaking the blinding to access the randomization schedule for a particular participant during the trial is not anticipated.

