Trained researchers administer the questionnaires (SCI, ISI, PSQI, BDI, and BAI). The data are entered into an electronic case-report form by a trained member of the research team. The following data points are collected:Demographics: date of birth, age, sex, employment statusCo-morbidities: history of diabetes mellitus, atrial fibrillation, dialysis, chronic renal disease, chronic kidney disease, congestive heart failure, dyslipidemia, nocturnal asthma attacks, peripheral vascular disease, current smoker (or smoked within last 6 months), mean number of cigarettes smoked per day, alcohol intake, caffeine intake, and level of physical activityResting heart rateBlood pressure (calibrated, identical machines are used on all participants)Office automated SBP (mm Hg)Office automated DBP (mm Hg)Mean 24-hour ambulatory SBP (mm Hg)Mean 24-hour ambulatory DBP (mm Hg)Daytime peak SBP (mm Hg)Daytime peak DBP (mm Hg)Nighttime peak SBP (mm Hg)Nighttime peak DBP (mm Hg)Mean daytime SBP (mm Hg)Mean daytime DBP (mm Hg)Mean nighttime SBP (mm Hg)Mean nighttime DBP (mm Hg)Current medications: – antihypertensives, statins, other lipid-lowering agents, antithrombotic therapy, oral hypoglycemic agents, insulin, sedatives/hypnotics, and analgesicsSleep questionnaires (PSQI, SCI, ISI)PSQI scorePSQI >5Time in bedSOLWASOTotal sleeping time (TST)Sleep efficiencySCI scoreSCI score ≤5.9ISI scoreISI score ≥15BAI scoreBDI scoreHeight, weight, BMI (calculated by using a standard automated weighing scale and a Leicester height measure)Laboratory measurements (nonfasting samples)Plasma lipoproteins: total cholesterol (TC), low-density lipoprotein cholesterol (LDL-C), high-density lipoprotein cholesterol (HDL-C), triglycerides (TGs), apolipoprotein B (ApoB), and apolipoprotein A1 (ApoA1)Plasma HbA1ceGFR

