#### Cointerventions

Participants in this trial will ideally not receive any antihypertensive medications throughout the 8-week period. However, participants receiving up to two antihypertensive agents at the time of entry into the trial are eligible for inclusion, provided that no recent (within the previous 8 weeks) changes occurred in type or dose of antihypertensive medications and there are no planned change to antihypertensive medication over the next 8 weeks (during the trial). Note: in patients with mild hypertension and no history of CVD, current guidelines recommend an initial period of lifestyle intervention, consistent with our approach. Treating clinicians will be permitted to use clinical judgment in initiating and dose-adjusting antihypertensive therapies for both study groups during the 8-week trial, where appropriate. Participants who are stable on cardiovascular preventive therapies (no change in previous 3 months), such as lipid-lowering agents, antithrombotic therapies, oral hypoglycemic agents, and insulin will continue their usual treatment. Participants not taking these agents will be encouraged to avoid initiation of treatment with these agents, until the 8-week trial period has been completed. However, treating clinicians will be permitted to use usual clinical judgment in initiating and dose-adjusting such medications, where appropriate. Initiation and/or dose adjusting of cointerventions will be recorded and measured and accounted for using sensitivity analysis. Participant adherence to the intervention will also be measured, and adjusted for using sensitivity analysis. For example, we will analyze the data for evidence of a dose/response relation between degree of reduction in SBP and number of online sleep sessions completed.

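### The stated blinding conflicts with the protocol's own use of online-session data: firmly for the statistician, depending on timing for site researchers, and probably for participants

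*Protocol article*

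**What the plan says.** The Protocol article makes the blinding claim in three sections.

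- Blinding: "Trial participants, investigators, data collectors, statistician, and outcome assessors are blinded to study-group assignment". One exception is given: "Members of the Sleepio team assigning participants to treatment groups are not blinded".
- Data collection and quality control: "All study personnel are blinded to study-group assignment and will remain blinded until all data have been collated". The sentence continues through data entry and review to completion of the analyses.
- Randomization: the statistician is named among those blinded, and unblinding follows the analyses.

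Other text bears on whether this can be so.

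- Data collection and quality control: "Data are entered into an electronic case-report form by the attending researcher", and the listed items include "adherence to follow-up, adherence to the intervention, and questionnaire scores".
- Cointerventions: adherence is to be measured, with the example of a "dose/response relation between degree of reduction in SBP and number of online sleep sessions completed".
- Statistical analysis: the primary dataset is on-treatment, defined by completion of one or more online sleep sessions. Intention-to-treat is secondary there, although the Abstract names it as the analysis.
- Subgroup and sensitivity analyses: adherence is both a subgroup factor and the subject of a sensitivity analysis.
- Measurements: "Trained researchers administer the questionnaires (SCI, ISI, PSQI, BDI, and BAI").
- Blinding, on the consent form and leaflet: "It is also mentioned that aspects of the intervention are delivered via online web sessions, as well as through face-to-face sessions".
- Randomization: the access code is sent to participants allocated to the online program. Controls get one 30-minute education session in week 1, and the Discussion says that no attention placebo is used.

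**The concern.** Session data exist for one arm only, so anyone who holds them at participant level holds the allocation. The protocol gives such data to two roles that it declares blinded, the statistician and the site researcher. It also gives participants enough information to work out their own group.

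Two things are at stake. First, researchers who may know the arm administer the sleep and mood questionnaires, and participants who may know it answer them. Results presented as blinded would then not be. Second, the Discussion itself says that awareness of assignment could lead to differential cointervention, and changes to antihypertensive therapy by treating clinicians are allowed during the 8 weeks. That route could reach the primary outcome.

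**Working it through.** No stated figure underlies the blinding claim. The check sets the sections side by side, role by role, and then counts the exposed outcomes.

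**1. Statistician.** Let *s* be the number of online sessions completed. Only the sleep arm receives a code and there are six sessions, so *s* = 0 for every control (assuming none obtains access) and *s* lies between 0 and 6 in the sleep arm.

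- *s* ≥ 1 means sleep arm, with certainty.
- *s* = 0 means either a control or a sleep-arm participant who never started. An on-treatment comparison that keeps controls must separate the two.
- Coded labels (A/B) do not help, because every non-zero count falls under one code.
- If an unblinded person supplied only an on-treatment flag, comparison with the intention-to-treat set, which is also planned, would show all never-started exclusions under one code. If nobody failed to start, the flag would reveal nothing, but the dose-response analysis would still need the counts.
- Scale: the protocol hopes for adherence above 85%. If adherent implies at least one session, then 0.85 × 67 = 56.95, so 57 or more of the 67 sleep-arm participants would be identified directly.

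The planned analyses therefore cannot be completed by a statistician who stays blinded until they are complete.

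**2. Attending researcher.** The adherence field and the claim that all personnel stay blinded stand in adjacent paragraphs of one section. Adherence could in principle mean attendance at the shared education session. However, the Cointerventions example counts online sleep sessions, and the section on maximizing adherence has the online team contacting those who fall behind. The effect depends on timing.

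- Entered before the 8-week measurements: the arm can be known to staff who then administer questionnaires, assuming that the same staff do both, which the article does not say.
- Entered afterwards: questionnaire administration is unaffected, but the claim that personnel stay blinded to the end of the analyses is still not met.

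**3. Participants.** All are told that an intervention is compared with a control and that part of it is online. The sleep arm then receives a code, six sessions, a daily sleep diary and optional reminders. Controls receive none of these. A sleep-arm participant can readily recognise the online part named in the leaflet. A control can notice its absence, but may take the face-to-face session for the intervention. This is a strong inference, not a contradiction in the text.

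**4. Exposed outcomes.** Secondary outcomes as listed:

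| Group | Number |
|---|---|
| 24-hour diastolic pressure | 1 |
| Daytime and nighttime pressures | 8 |
| BMI | 1 |
| Lipoproteins | 6 |
| HbA1c, eGFR | 2 |
| Smoking status, cigarettes per day | 2 |
| SCI, ISI, PSQI, SOL, WASO, total sleep time, sleep efficiency | 7 |
| Sleep-threshold proportions | 5 |
| BDI, BAI | 2 |
| **Total** | **34** |

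Self-reported sleep and mood: 7 + 5 + 2 = 14, and 14/34 = 41%. SOL, WASO, total sleep time and sleep efficiency are counted because Measurements lists them with the sleep questionnaires. The two smoking outcomes are probably self-reported as well, but the article does not say so and they are left out.

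**The case against.** The strongest defence is that the masking is deliberate and its limits are disclosed. The leaflet presents the intervention as general cardiovascular education, partly online and partly face-to-face, and controls do attend a face-to-face session, so some may believe they are in the intervention group. The Discussion names awareness of assignment as its first limitation, and also names attention bias and explains the lack of an attention placebo. Cointerventions says that drug changes will be recorded and addressed by sensitivity analysis. Session data arise in the web application, so site entry may come late. The primary outcome is an automated 24-hour reading.

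Much of this stands. It is why the participant point is put as likely and the researcher point as dependent on timing. A reader might infer that nobody in this trial is blinded, or that the primary result is biased. The documents support neither. Automated measurement protects systolic pressure from observer bias, nothing shows that adherence is entered before the 8-week visit, and differential cointervention is a risk that the plan already means to examine.

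The defence does not remove the conflict. The only stated measure against unmasking is to present the sleep questionnaire as one of several routine baseline screens. That does not touch session counts, the adherence field or the access code. Acknowledging a risk also does not reconcile an unqualified claim with text that contradicts it.

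**Conclusion.** The blinding statements should be corrected. The strength differs by role.

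- **Statistician: firm.** The on-treatment, dose-response and adherence analyses cannot be run without data that identify the sleep arm. This rests only on controls having no access to the online program.
- **Attending researcher: firm as written, consequence open.** The adherence field is inconsistent with personnel blinded to the end of the analyses. It can affect outcome measurement only if it is filled in before the 8-week questionnaires.
- **Participants: likely, not certain.** Many can infer their arm. At most, they are unaware that sleep is the hypothesis, which is not the same as blinding to group.

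The exposure covers 14 of 34 secondary outcomes. For the primary outcome, the remaining risk is differential cointervention, whose size the documents do not allow one to estimate.

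**What to change.** 1. Remove adherence to the intervention from the fields entered by site researchers.
2. Keep session counts with the online-intervention team, which is already unblinded. Release them only after all 8-week outcome data have been entered, reviewed and locked.
3. Limit the statistician's blinding claim to analyses that do not use session data. This covers the primary analysis only if that is intention-to-treat, as the Abstract states. The Statistical analysis section makes on-treatment primary, so the two must be reconciled separately. This point does not settle which one governs.
4. Describe participants as not told the sleep hypothesis, instead of as blinded to group.
5. Report the 14 self-reported sleep and mood outcomes as not participant-blinded.

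A switch to self-completed questionnaires at 8 weeks is not recommended. Baseline is researcher-administered and recruitment is under way, so the mode would change between the two ends of a change score. It would also do nothing about participants who know their arm.

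The cost is a change to the case-report form and to the data-transfer wording. Adherence data will be cleaned later, and the description of blinding becomes less favourable.

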## Discussion

### Methods of minimizing bias

One potential limitation of this study is the risk of contamination, if participants or clinicians become aware of individual treatment-group assignments. This could result in the differential use of co-interventions between the two study groups, or use of a sleep intervention in the control group, resulting in bias toward the null. The screening questionnaire for sleep quality is another potential source of unblinding. To minimize the risk of unblinding, it is being administered as a routine baseline screen, along with questionnaires to measure depression, anxiety, and cognitive function.

A second potential limitation is volunteer bias. Individuals who participate in studies are often more healthy than those who refuse to provide consent. Thus, the actual sample of individuals included in the trial may not be representative of the relevant population, limiting the generalizability of the results. Furthermore, study volunteers are often well-motivated, highly adherent individuals who are likely to benefit from such an intervention. This would also affect the external validity of the results. However, this is a proof-of-concept, phase II study, and such a population will maximize the chances of detecting the true treatment effect, before testing the effectiveness of this intervention in a wider population.

A third potential limitation in this study is the primary outcome measure of reduction in mean 24-hour systolic blood pressure, which is a surrogate outcome measure. As this is a pilot study, a clinical outcome would not be feasible, as a relatively long follow-up period would be required to demonstrate a treatment effect. Reduction in blood pressure has been shown to be predictive of significant reductions in major vascular events. Thus, we believe that reduction of systolic blood pressure is an appropriate outcome measure for this study.

A fourth potential limitation of this study is the risk of nonadherence to the intervention, which is a particular challenge in trials evaluating behavioral interventions. However, a number of measures are being implemented to maximize adherence (see earlier). To determine the influence of adherence on the estimated treatment effect, a sensitivity analysis will be performed.

A fifth potential limitation is that patients with undiagnosed OSA may be included in this study, which could undermine our ability to detect a true treatment effect, given that such patients may not be expected to improve with the intervention. Thus, we have excluded patients with a known diagnosis of treated OSA, to minimize this potential limitation. Finally, our results could be subject to attention bias, due to differences in the level of attention provided to the two treatment groups. However, given that this is a phase II, proof-of-concept study, with the aim of maximizing the chances of detecting a true treatment effect, we elected not to use an attention placebo in the control arm. If a significant treatment effect is observed in this pilot study, a larger-scale phase III trial will be performed, with the inclusion of an attention placebo in the control arm, to demonstrate the effectiveness of this intervention in a broader population of patients for primary and secondary prevention of CVD.

## Trial status

Ongoing, participant recruitment under way.

## Abbreviations

ApoA1: Apolipoprotein A1
Apo B: Apolipoprotein B
BAI: Beck Anxiety Inventory
BDI: Beck Depression Inventory
BMI: Body mass index
CVD: Cardiovascular disease
DBP: Diastolic blood pressure
eGFR: Estimated glomerular filtration rate
GUH: Galway University Hospital
HRB-CRFG: Health Research Board-Clinical Research Facility Galway
ISI: Insomnia Severity Index
HDL-C: High-density lipoprotein cholesterol
LDL-C: Low-density lipoprotein cholesterol
OSA: Obstructive sleep apnea
PSQI: Pittsburgh Sleep Quality Index
SOL: Sleep-onset latency
SBP: Systolic blood pressure
SCI: Sleep condition indicator
SD: Standard deviation. TC, total cholesterol
TG: Triglyceride
TST: Total sleep time
WASO: Wake time to sleep onset.
